Frontal alpha asymmetry (FAA) is typically investigated in relation to emotional response and motivations, both in clinical and normal populations [10]. Left-lateralized or left-dominant brain activity has been linked to an *approach* system where an individual experiences positive emotions and motivations. In contrast, right-lateralized frontal activity may reflect negative emotions and intention to withdraw. Reduced alpha power in the left frontal area of the scalp in individuals with ASD has also been reported [9]. The modulation of FAA has been demonstrated in neurofeedback training in individuals with ASD to activate their imitation behaviors [11, 12], so this measure is hypothesized to predict and be responsive to social skill interventions. High-functioning individuals with ASD show intact emotional processing when listening to music, although they demonstrate distinct neural patterns relative to neurotypical adults, which is interpreted as increased cognitive load and physiological arousal [13]. Individual preference for music varies within the target group with ASD and ID and may predict how they respond to social skill intervention using music therapy. Although self-report rating scales exist for reporting music experience and preference, qEEG measures may be superior because they index automatic responses to musical stimuli that the target population of children with ASD and ID may find difficult to understand or express.

The proposed study will address the research gap on music therapy as an intervention for social functioning in children with ASD with mild to borderline ID. The research design is to examine whether using music therapy as social skill intervention provides additional benefits relative to non-musical active control behavioral intervention in a 12-week RCT. We will also evaluate whether pre-treatment neural response to music is correlated with the effectiveness of musical social skill intervention. If correlation is found, then the long-term goal is to develop individualized intervention based on pre-treatment markers to maximize treatment efficacy.

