### Objectives

Aims and hypotheses to be tested:
On the group level, is social skill intervention using music therapy more effective in enhancing social interaction than non-musical social skill training for children with ASD and co-occurring mild/borderline ID?On the individual level, are participants with enhanced left-lateralized FAA to social scenes relative to baseline more responsive to both types of social skill interventions?For participants in the music therapy intervention, does enhanced left-lateralized FAA to preferred music relative to baseline predict better outcomes in social skill development?

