#### Secondary outcomes

EEG will be recorded using Epoc X (EMOTIV) research-grade EEG headsets with 14 channels digitized at 256 Hz. This tool is a child-friendly wireless mobile EEG system that is easy to apply with non-sticky saline-based wet sensors and has high research quality [16]. The data collection will be conducted by research assistants who are blinded to the participants’ group assignment. Recording will be performed in three conditions, namely, resting state, social scenes, and preferred music, for 5 min each. For the baseline resting state condition, data will be recorded with participants at rest, passively viewing an animation of moving shapes without sound. Although resting-state qEEG in adults is usually measured without explicit sensory stimulation, a simple viewing task is used here because it will be difficult for children to sit still without anything to hold their attention [16]. For the social scene condition, participants will view typical scenes where children or adults interact in school and playground without sound. For the preferred music condition, the participants will listen to their preferred music with eyes opened and fixated on a cross on a computer screen.

To determine the music preference of participants, a brief selection task of 25 different music pieces and genres will be administered, based on a task adapted from previous research reporting a five-factor music preference model called MUSIC [20]. Each music excerpt will be 15 s long, and participants will indicate their preference for each piece based on a 5-point pictorial scale. The dominant music style will be calculated for each participant and 5 min of preferred music pieces will be played to obtain neural responses to music in the pre-test and post-tests.

EEG segments free of artifacts will be selected, and spectrum decomposition will be carried out. Absolute and relative power levels in different frequency bands (alpha, beta, delta, gamma, and theta) will be calculated in each condition. FAA index will be calculated by subtracting the alpha frequency power from left and right frontal electrodes. The difference in FAA in the social scenes and baseline will be used as a predictor in data modeling in treatment and control groups. The FAA in preferred music condition will be correlated with treatment effectiveness in the treatment group only.

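### The stated music-FAA analysis omits the baseline subtraction that objective 3 asks for, its arm scope conflicts between two sections, and a music-arm correlation alone cannot support treatment selection

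*Protocol article*

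**What the plan says.** The third aim under Objectives in the protocol article reads: "For participants in the music therapy intervention, does enhanced left-lateralized FAA to preferred music relative to baseline predict better outcomes in social skill development". It fixes both the population (the music arm) and the predictor (a contrast with baseline).

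Secondary outcomes describes the recordings: "Recording will be performed in three conditions, namely, resting state, social scenes, and preferred music, for 5 min each". It calls the resting state the baseline condition and does not limit the music recording to one arm. It then defines the two predictors in consecutive sentences. For social scenes: "The difference in FAA in the social scenes and baseline will be used as a predictor in data modeling in treatment and control groups". For music: "The FAA in preferred music condition will be correlated with treatment effectiveness in the treatment group only".

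Statistical analyses lists the fixed-effect predictors of the mixed model. Pre-treatment frontal asymmetry, social and music, stands there beside intervention type and time. The list gives no arm restriction, no difference from baseline and no FAA-by-arm term.

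On the use of such a marker, Prediction of treatment success says that, if a correlation is found, "the long-term goal is to develop individualized intervention based on pre-treatment markers to maximize treatment efficacy". The Discussion likewise says, conditionally, that pre-treatment markers could help to identify suitable intervention plans.

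**The concern.** There are three linked problems.

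1. **Predictor.** Objective 3 concerns how FAA changes when preferred music is played. FAA in the music condition alone also carries whatever asymmetry the child shows at rest. An analyst who follows Secondary outcomes to the letter answers a different question from the one posed, and the neighbouring sentence shows that the authors know how to state the subtraction.

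2. **Arm scope.** Secondary outcomes confines music FAA to the treatment group, while Statistical analyses puts it in a model that contains intervention type, hence both arms. These are two different analyses of the same predictor.

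3. **Inference.** A correlation within the music arm shows that children with a given FAA do better under music therapy. It does not show that they do better than they would have under the control training. Only the latter supports choosing an intervention by FAA. A positive music-arm result could be carried forward as a selection marker when FAA has no bearing on which intervention works.

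**Working it through.** The plan gives no figure for the FAA analyses. From the document come 40 children per arm and 25% attrition, so 40 × (1 − 0.25) = 30 per arm. The correlations below are assumptions, shown over a range, because the document gives none. All tests are two-sided at 0.05.

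**Raw versus baseline-corrected FAA.** Let M be FAA to music and B resting FAA, with equal variance σ² and correlation ρ. Then Cov(M, M − B) = σ²(1 − ρ) and Var(M − B) = 2σ²(1 − ρ), so corr(M, M − B) = √((1 − ρ)/2).

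Suppose that the outcome correlates 0.5 with M − B and is related to M only through that difference. The raw predictor then shows 0.5 × √((1 − ρ)/2). Fisher-z power is Φ(atanh(r)·√(n − 3) − 1.96), here with n = 40.

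| Assumed ρ | corr(M, M − B) | r seen with raw M | Power, n = 40 |
|---|---|---|---|
| 0.5 | 0.50 | 0.25 | 34% |
| 0.7 | 0.39 | 0.19 | 22% |
| 0.9 | 0.22 | 0.11 | 10% |

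With the correct predictor (r = 0.5) power is 92%.

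**Sensitivity of the one-arm correlation.** For 80% power it needs r = tanh((1.96 + 0.84)/√(n − 3)), about 0.43 at n = 40 and 0.49 at n = 30.

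**Purely prognostic marker.** Suppose that FAA relates to outcome equally in both arms, so that it says nothing about which intervention to choose. For r = 0.3 and n = 40: atanh(0.3) = 0.3095, times √37 = 6.083 gives 1.883, minus 1.96 gives −0.077, and Φ = 0.47. The last column comes from a simulation of 4,000 trials per setting: standard normal FAA, unit-variance outcome, and a linear model with arm, FAA and their product.

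| r in both arms | Music-arm correlation significant, n = 40 | Same, n = 30 | FAA-by-arm term significant |
|---|---|---|---|
| 0.3 | 47% | 36% | 4–5% |
| 0.4 | 73% | 60% | 5% |
| 0.5 | 92% | 81% | 4–5% |

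**Marker specific to music.** With the correlation in the music arm only, the same simulation gives these powers for the FAA-by-arm term:

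| r in music arm, 0 in control | 40 per arm | 30 per arm |
|---|---|---|
| 0.4 | 43% | 33% |
| 0.5 | 62% | 50% |

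The simulation treats children as independent and ignores the training groups of eight and the covariates.

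**The case against.** **The music-arm restriction is what objective 3 says.** This stands. A reader might infer that analysing one arm departs from the objective, but the aim is worded for participants in the music therapy intervention. Only the missing subtraction departs from it. For that objective the 47% and 36% are correct positives. They become errors only if the result is read as a guide to choosing between interventions.

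**Individualised treatment is a conditional, long-term goal.** This also stands. Nothing in the article says that this trial will license assignment by FAA. The point about prognosis is therefore a limit on interpretation, not a breach of a stated aim.

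**The article is condensed, and interaction terms may be left to an analysis plan.** This stands in part. The absence of an FAA-by-arm term from the list does not show that one was rejected, and it is not counted here as an omission. It does not excuse two adjacent sentences that define parallel predictors differently, or two sections that disagree on arm scope.

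**Resting asymmetry.** A reader might infer that it is known to contaminate the raw predictor. The document gives no rest–music correlation, so the size is assumed. Nor is the difference free of it: under the same assumptions, M − B correlates −√((1 − ρ)/2) with B.

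**The visual stimulus.** A reader might infer that music minus rest is itself invalid, because rest uses moving shapes while for music "the participants will listen to their preferred music with eyes opened and fixated on a cross on a computer screen". The document does not support this. Its remark that "it will be difficult for children to sit still without anything to hold their attention" explains the resting condition and speaks of difficulty, not impossibility. Music may itself hold attention. A visual difference common to all children need not bias a predictor that compares children, and an animation during the music could distract from it. No change of stimulus is called for.

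**Conclusion.** The point holds in three parts of unequal weight. The firmest is textual and rests on no assumption: objective 3 asks about music FAA relative to baseline, Secondary outcomes analyses music FAA without it, and Statistical analyses does not restore it. The two predictors may be only weakly related (correlation 0.50 to 0.22), given equal variances and an assumed ρ of 0.5 to 0.9. Second, the two sections contradict each other on whether music FAA is analysed in one arm or both. Third, the within-arm correlation suits objective 3 but cannot carry a treatment-selection claim: a marker that is only prognostic, at an assumed r of 0.3 in both arms, would reach significance in the music arm 47% of the time with 40 children and 36% with 30. This is a secondary EEG analysis and leaves the group comparison untouched, but it bears on a named objective and should be corrected.

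**What to change.** - In Secondary outcomes, define the music predictor as pre-treatment FAA in the music condition minus pre-treatment FAA at rest, parallel to the social-scene predictor.
- Reconcile Secondary outcomes with Statistical analyses on arm scope. One model in all randomised children with an FAA-by-arm term serves both: it gives the slope within the music arm and the difference in slopes. With repeated outcomes, these terms are crossed with time.
- Keep the within-music-arm slope as the answer to objective 3.
- Label the FAA-by-arm term exploratory, and state that any claim about choosing music therapy by FAA must rest on it.

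The cost is a change of wording. Resting and music EEG are already planned, and the music recording is not limited to one arm, so no further recordings are needed. The downside is power. With equal arms, the standard error of a difference in slopes is √2, about 1.4 times, that of one slope. At roughly 43% power with 40 per arm and 33% with 30 (r = 0.4 in the music arm only), a null interaction would say little and should be reported with its confidence interval.

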### Statistical analyses

Interim analyses will not be performed and data collection will continue until the intended sample size is reached. The investigators and research assistants will have full access to the final trial dataset. Analyses will focus on hypothesis-driven testing with separate models for each outcome measure by using linear mixed effect modeling if the assumptions for linear effects are met [21]. This regression-based statistical test can be used to evaluate multiple categorical and continuous predictors, and eliminates the need to run multiple tests for different hypotheses, which inflates the risk for type I error. Attrition bias will be assessed by comparing the participant completion rate in the two conditions and considering the reasons. Mixed effect models are robust with missing or extreme values, which is useful if the attrition rate for the 12-week intervention is higher than expected. Fixed effect predictors will be intervention type (music/non-music), time (pre−/post-intervention), and pre-treatment EEG frontal asymmetry (social and music). The random effects of participants and groups will be included to estimate random errors arising from individual differences in participants and group trainers. Control factors will include overall and verbal IQ, age, and ASD severity. The inclusion of these covariates alleviates concerns on unreliable effects due to the heterogeneity of children with ASD and ID.

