**Method:**

A randomized controlled trial (RCT) with two parallel groups of 40 children each (1:1 allocation ratio) is planned. Participants will receive 45 min of music therapy or non-musical intervention targeting social skills once a week for 12 weeks. Primary outcome measures will be independent ratings on the Childhood Autism Rating Scale and parent ratings on the Social Responsiveness Scale-2. Linear mixed-effects models for these two outcome measures will be created for data collected at 2-week pre-intervention, 2-week post-intervention, and 4-month post-intervention sessions. In-session behaviors at the first and last intervention will be videotaped and coded offline and compared. Pretreatment neural response of quantitative electroencephalograms (qEEG) to social scenes will be used to predict the outcomes of musical and non-musical social skill interventions, whereas qEEG responses to music will be used to predict the effectiveness of musical social skill intervention.

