### Outcome measures

#### Primary outcomes

The primary outcome measure is autistic severity as assessed using a standardized rating scale by an independent rater who will be blinded to the study group allocation. This outcome was selected because observing behavioral changes that generalize to other social contexts outside of the intervention is the ultimate goal of social skill intervention. Parental rating by using a standardized rating scale is included as another outcome to support the clinical assessment. Parents are good informants because they spend time with the participants outside of intervention contexts, but they are not blinded to the group assignment and may exhibit expectation biases. Another outcome is the behavioral changes at the last intervention sessions relative to the first session. Trained research assistants who are blinded to the session number and study hypotheses will code for target social behaviors by using video data. This measurement will provide an objective measure of the social skills exhibited by participants within the intervention setting.

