##### In-session social behavior

The intervention sessions in the treatment and control groups will be videotaped using a high-resolution video camera, and data from the first and last sessions will be coded for target social behavior. The three main types of behavior, namely, initiation, turn taking, and eye contact, will be examined using a microanalysis of video recordings in one-second intervals [19]. Target social skills were selected based on the expected types of behavior that may occur during the sessions and that are essential for effective social interactions. The frequency and duration of the social behavior will be recorded with the following coding scheme. Initiation includes touching a person, making a verbal request, giving an object to a person, and other actions to get another’s attention. Turn taking includes responding within an appropriate time either verbally or non-verbally and not interrupting out of turn. Eye contact includes directing the gaze toward the person speaking or acting. The behavior will be further categorized as instructor-to-participant social interactions or participant-to-participant social interactions. Inter-rater reliability will be determined in 20% of coding. These behavioral outcomes are important indices of how much and how appropriately children engage in social interactions. Video data from each session will also be used to indicate the amount of explicit instruction (talking time of the trainer) and amount of music use, to validate the fidelity of the interventions. These data may be included as covariates in data analyses if they are significantly different across groups.

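### The plan names two primary outcomes in one place and one in another, and credits the mixed model with a type I error control it does not provide

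*Protocol article*

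**What the plan says.** The protocol article describes the primary outcome in three places that do not agree.

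- **Abstract, Method:** "Primary outcome measures will be independent ratings on the Childhood Autism Rating Scale and parent ratings on the Social Responsiveness Scale-2". This is plural, and the two measures are given equal standing.
- **Outcome measures, Primary outcomes:** "The primary outcome measure is autistic severity as assessed using a standardized rating scale by an independent rater". This is singular, and the rater is blinded to allocation. Of the parent scale it says: "Parental rating by using a standardized rating scale is included as another outcome to support the clinical assessment". It adds that parents know the assignment and may be biased by what they expect. It then goes on: "Another outcome is the behavioral changes at the last intervention sessions relative to the first session".
- **Layout of the outcomes section:** CARS-2, SRS-2 and in-session social behaviour each have a subsection under the Primary outcomes heading. Only EEG is listed under Secondary outcomes.

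The Statistical analyses section announces "hypothesis-driven testing with separate models for each outcome measure", using linear mixed-effects models. It then describes the method as able to handle several categorical and continuous predictors, and says that it "eliminates the need to run multiple tests for different hypotheses, which inflates the risk for type I error".

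An alpha of 0.05 appears once, in Sample size calculation, for a two-group t statistic.

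**The concern.** The primary outcome decides what counts as success. Under the abstract, a positive parent rating could carry the trial. Under the Primary outcomes section it could only support a blinded clinical rating. The difference matters because the article itself says that the parents are unblinded and open to bias. If both descriptions stand, the choice between them can be made after the results are known.

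The type I error sentence makes this worse. It tells the reader that the modelling approach has dealt with multiple testing, and so could be cited as the reason for having no rule when two outcomes are both reported as primary.

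**Working it through.** **1. The plan's own sample size.** Inputs from Sample size calculation: standardized effect 0.71, alpha 0.05, power 0.8, attrition 25%, result 33 per group. Sidedness is not stated.

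- Two-sided, normal approximation: n = 2 × ((1.960 + 0.842) / 0.71)² = 31.1, so 32 per group. The t-test solution is 32.13, so 33. This matches the stated figure before attrition.
- One-sided, normal approximation, with attrition: 24.53 / 0.75 = 32.7, so 33 if rounded only at the end.

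Whether attrition is really included in the 33 is a separate question. By either route the figure is for one comparison at 0.05, with no allowance for a second or third primary outcome.

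**2. Does the mixed model remove multiplicity?**

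- *Across outcomes:* one model per outcome means at least one treatment test per outcome. Nothing in a model for CARS-2 limits the error rate in a model for SRS-2.
- *Within one model:* the listed fixed effects include intervention type, time and two EEG asymmetry measures. Each coefficient has its own test at its own level. Fitting them jointly adjusts the estimates for one another but does not hold the combined error rate at 0.05.

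The sentence is therefore incorrect on either reading.

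**3. Size, if any one outcome counts as success.** Assume a two-sided test at 0.05 for each of k outcomes.

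Independent: 1 − 0.95^k. For k = 2 this is 1 − 0.9025 = 0.0975. For k = 3 it is 1 − 0.857375 = 0.1426.

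Correlated: the probability that the largest of k equicorrelated standard normal statistics exceeds 1.960 in absolute value, by simulation with 2,000,000 draws. The documents give no correlation, so a range is shown.

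| Assumed correlation | Two outcomes | Three outcomes |
|---|---|---|
| 0 (exact) | 0.0975 | 0.1426 |
| 0.3 | 0.095 | 0.136 |
| 0.5 | 0.091 | 0.125 |
| 0.7 | 0.084 | 0.109 |
| 0.9 | 0.070 | 0.083 |

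**4. What a rule for several primaries would cost.** Take the planned 40 per group and the stated 25% attrition: 40 × 0.75 = 30 evaluable. The figures are for a simple two-sided t-test with effect 0.71 on every outcome, ignoring covariates and the treatment groups of eight.

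| Number of primaries (Bonferroni) | Alpha each | Power with 30 per group | Evaluable per group for 80% power | Recruited per group at 25% attrition |
|---|---|---|---|---|
| One | 0.05 | 0.77 | 33 | 44 |
| Two | 0.025 | 0.67 | 39 | 52 |
| Three | 0.0167 | 0.61 | 43 | 58 |

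If instead both of two outcomes had to succeed, alpha would not inflate but joint power would fall. With 0.77 each and independence it would be 0.77² ≈ 0.59, and at most 0.77 under perfect correlation.

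**The case against.** **The sentence is about predictors.** It follows a remark on handling several predictors, and the hypotheses it means may be the three aims: intervention type, EEG response to social scenes and EEG response to music. The same section openly plans separate models per outcome. This reading is fair, and one should not say that the authors expressly claim to have removed multiplicity across outcomes. It does not rescue the sentence, because several coefficients in one model are still several tests.

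**The level per outcome is not stated.** This is true. The 0.05 is carried over from the sample size section, and the inflation figures also assume that either outcome alone would count as success, which the article does not say. A multiplicity rule could sit in an analysis plan that is not shown, so the point is not that an adjustment is missing. A later document would still have to contradict either the abstract or the Primary outcomes section.

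**Three primary outcomes.** A reader might infer three from the heading. That rests on layout alone: no sentence calls in-session behaviour primary, and the abstract lists it apart from the primary measures. The figures for three show only what would follow if the heading were taken literally.

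**A much larger inflation.** The in-session subsection names "The three main types of behavior, namely, initiation, turn taking, and eye contact", codes frequency and duration, and splits by interaction partner. That gives 3 × 2 × 2 = 12 measures. Adding CARS-2 and SRS-2 as independent tests would give 1 − 0.95^14 = 51%. The documents do not support that figure: this is a coding scheme, no section plans 12 tests, and frequency and duration of the same behaviour in the same child are unlikely to be independent.

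**In-session behaviour as a comparison between arms.** One might also object that activities differ by arm and that the first session is already treatment. The article says that "data from the first and last sessions will be coded for target social behavior" and describes the outcome as change between those sessions. It makes no explicit between-arm claim for it, claims coder blinding to session number and hypotheses but not to arm, and allows trainer talk and music use as covariates. That is a different question and is not part of this point.

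**CARS-2 is not the only possible choice.** The 0.71 comes from generalized social interaction, the term the SRS-2 subsection uses for the parent rating, whereas the CARS-2 subsection speaks of general autistic symptoms. This stands as a caution for the fix.

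**Conclusion.** The point holds. The article contradicts itself on whether there are one or two primary outcomes, and its heading blurs the matter further by including in-session behaviour. The statement about type I error is incorrect for separate outcome models and for several coefficients within one model.

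If either CARS-2 or SRS-2 could establish success at 0.05, the family-wise error would be 9.75% under independence and about 8.4% at a correlation of 0.7. Taking the heading literally, it would be 14.3% and 10.9% for three outcomes. These figures rest on an inferred alpha, two-sided tests, an any-success rule and assumed correlations. The contradiction and the incorrect sentence rest on none of these. The sample size is for a single comparison, so it fits one primary outcome and not several.

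This should be corrected before results are known, because as written the unblinded parent scale could be presented as the trial's primary success.

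**What to change.** 1. Name one primary outcome in the abstract, the outcomes section and the analysis section. Blinded CARS-2 is the choice that agrees with the Primary outcomes section. State one primary time point: the abstract models visits at 2 weeks and 4 months after intervention, while the analysis section gives time only as before and after.
2. List SRS-2 as a supportive secondary outcome. If two primaries are really meant, state whether both must succeed or alpha is split, and restate the power.
3. Move in-session behaviour out of the Primary outcomes heading.
4. Delete the type I error sentence, or limit it to saying that the model estimates several predictors jointly.
5. With CARS-2 as primary, add a line on why the effect of 0.71 is taken to apply to it.

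The cost is wording in four sections, and SRS-2 can no longer establish success on its own. Keeping two primaries costs more: with an alpha split and 30 evaluable per group, power for each outcome falls from 0.77 to 0.67, and 80% power would need 52 recruited per group instead of 40.

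### Pre-treatment frontal alpha asymmetry (FAA) is a fixed effect in the model that carries music versus non-music, so a fit as written without imputation leaves out fully rated children who lack usable baseline EEG

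*Protocol article*

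**What the plan says.** All of this is in the protocol article.

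- **Statistical analyses, model structure.** "Analyses will focus on hypothesis-driven testing with separate models for each outcome measure by using linear mixed effect modeling". The models are divided by outcome, not by aim.
- **Statistical analyses, predictors.** There is one list: "Fixed effect predictors will be intervention type (music/non-music", then time, "and pre-treatment EEG frontal asymmetry (social and music". Random effects for participants and groups follow, with IQ, age and ASD severity as control factors.
- **Statistical analyses, rationale.** The regression approach is said to be an advantage because it "eliminates the need to run multiple tests for different hypotheses, which inflates the risk for type I error".
- **Statistical analyses, missing data.** "Mixed effect models are robust with missing or extreme values, which is useful if the attrition rate for the 12-week intervention is higher than expected".
- **Secondary outcomes.** EEG is recorded for 5 minutes in each of three conditions: rest, social scenes and preferred music. Then "EEG segments free of artifacts will be selected, and spectrum decomposition will be carried out". The social-minus-rest difference in FAA is a predictor in both arms. Music FAA is to be correlated with effectiveness in the treatment group alone.
- **Objectives.** The first aim is the group-level comparison of music with non-music. The second and third concern FAA to social scenes (both interventions) and FAA to preferred music (music arm).

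**The concern.** A likelihood-based mixed model keeps a child who misses an outcome visit. Unless a missing fixed-effect covariate is imputed, the same model omits every record of the child who lacks it. The article's one remark on missing values is tied to attrition during the intervention. It answers the first problem and not the second.

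Social FAA needs two usable recordings, rest and social scenes. Music FAA needs the music recording, and also the resting one under the wording of the third aim. A child may complete every rating and still lack one of these. As written, that child's CARS-2 and SRS-2 data would then not enter the main treatment comparison, for want of a measurement that the comparison does not use. The first aim would be answered in children with usable EEG and not in all randomised children, and the sample size makes no allowance for that loss.

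**Working it through.** **1. What the text fixes.** Two statements have to be read together: models are separate for each outcome, and the fixed effects come in a single list containing both the treatment term and FAA. No model without FAA is described for CARS-2 or SRS-2, and no imputation of a baseline predictor is mentioned.

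**2. The conflict on music FAA.** Secondary outcomes confines this measure to the treatment group. Statistical analyses places it beside intervention type in a model that spans both arms. The recordings are not described as limited to one arm, so values should exist for controls. The conflict is about how the measure is used. A main effect in a two-arm model uses it in both arms; a treatment-group correlation does not. One equation cannot follow both sections.

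**3. The plan's own sample size.** Inputs from Sample size calculation: d = 0.71, alpha 0.05 (sidedness not stated), power 0.80, attrition 25%, stated minimum 33 per group, 40 per group planned.

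- Two-sided t-test: n = 32.13, so 33 per group before attrition. Dividing by 0.75 gives 33/0.75 = 44 (43 from the normal approximation, 32/0.75).
- One-sided t-test: n = 25.23, so 26 before attrition and 26/0.75 = 34.7, so 35 (34 from the normal approximation, 25/0.75).

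The stated 33 therefore matches a two-sided test before attrition, or comes within two of a one-sided test after it. The checks below use the planned 40 per arm and a two-sided test.

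**4. Power if children without EEG are omitted.** The share without usable EEG is an assumption, because the article gives none. Per-arm n = 40 × (1 − attrition) × (1 − EEG loss); power is from a two-sided t-test at d = 0.71. The standard error rises by the factor √(1/(1 − EEG loss)).

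| EEG loss (assumed) | n, no attrition | Power | n, 25% attrition | Power | SE factor |
|---|---|---|---|---|---|
| 0% | 40 | 0.880 | 30 | 0.772 | 1.00 |
| 10% | 36 | 0.844 | 27 | 0.726 | 1.05 |
| 20% | 32 | 0.798 | 24 | 0.673 | 1.12 |
| 30% | 28 | 0.742 | 21 | 0.612 | 1.20 |

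The drop from 0.880 to 0.772 in the first row is due to attrition, not EEG. Only the movement down each power column belongs to this point.

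**5. Could FAA repay the loss as a prognostic covariate?** To a first approximation, the variance of the treatment effect is multiplied by (1 − R²)/(1 − EEG loss), where R² is the share of residual outcome variance that FAA explains. Setting this to 1 gives R² = EEG loss. At 10%, 20% or 30% loss, FAA would have to explain 10%, 20% or 30% of the residual variance just to break even. The article gives no figure for R².

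**The case against.** **Deletion is not stated.** This is correct. Omission of children is the default of a complete-case fit, and the article does not announce it. An analysis plan that is not shown could impute FAA or add a model without it. The point is therefore conditional on fitting the model as written. It is more than an omission, however, because the article does state a model and that model includes FAA.

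**The list may be an inventory of predictors across all three aims.** This reading is possible. The abstract puts the mixed models and the EEG prediction in different sentences, and the treatment-group-only use of music FAA sits badly with one equation. But the Statistical analyses section says that models are separate by outcome and that the approach "eliminates the need to run multiple tests for different hypotheses". If separate models are intended, the text should say so, and the fix costs almost nothing.

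**The article does not predict EEG failure.** This stands. The remark that "it will be difficult for children to sit still without anything to hold their attention" explains why an animation was added at rest; it describes a mitigation. The headset is also presented as child-friendly. The remark shows that cooperation was a consideration and supports no failure rate.

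**The power figures after attrition are pessimistic.** This stands in part. A mixed model retains children who leave after baseline, so 30 per arm understates the information available. Multiplying the two losses also treats them as unrelated; if the same children fail both, the added loss is smaller. For this reason both bases are shown. From 40 per arm, 20% loss still gives about 0.80.

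**FAA adjustment might gain precision.** It might, so the net effect is unknown; step 5 of the working shows what it would have to achieve.

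**Conclusion.** The concern holds in conditional form. The article places FAA in the per-outcome model that tests music against non-music and offers no FAA-free model for the first aim. Its remark on missing values does not reach a missing baseline predictor. Fitted as written without imputation, fully rated children without usable baseline EEG would be left out of a comparison that needs no EEG.

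The size rests on an assumed 10–30% of children without usable EEG. Over that range power is 0.84–0.74 instead of 0.88 with no attrition, or 0.73–0.61 instead of 0.77 after 25% attrition. The calculation is a simple two-group t-test that ignores repeated measures, covariates and clustering in groups of eight.

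A reader might infer three stronger claims, and the article supports none of them:

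- **That these children will certainly be dropped.** The article does not specify how missing covariates are handled.
- **That those remaining would be calmer, less severe or less sensory-sensitive.** This is plausible, but nothing in the article documents the direction of selection.
- **That the comparison between arms would be biased.** The relevant EEG is recorded before the intervention by staff blinded to group, so loss should be similar in the two arms. The foreseeable harm is to precision and to the population analysed.

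**What to change.** 1. Fit the first-aim model for CARS-2 and SRS-2 with no EEG terms, on all randomised children with at least one rating.
2. Test social FAA (both arms) and music FAA (music arm only) in separate secondary models, on children with usable EEG. Report how many children each model excludes.
3. Reconcile Secondary outcomes with Statistical analyses on where music FAA is used.

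The cost is a change of analysis wording and one or two additional models. No new data are needed. The statement that the approach removes the need for multiple tests has to be dropped, since the aims would then be tested in separate models.
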